### Identification, Measurement, and Valuation of Benefits

For QALY estimations, self-reported health-related quality of life (HRQoL) data were collected from patients or their proxy at 3- and 12-months using the EQ-5D-3L questionnaire (15, 16). The most appropriate published algorithm to convert the responses into utility values for an Australian population will be used (17). The Assessment of Quality of Life tool (AQoL-4D) (18), which has been validated in an Australian population of stroke survivors (19), was also collected in order to provide alternate utility values for sensitivity analyses.

Functional status was assessed using the modified Rankin scale (mRS) (20, 21). This was collected as a measure of the patient's functional status before stroke (obtained from health status information recorded at time of admission), at discharge (days 7–10, or on day of discharge if before day 7), as well as at 3- and 12-months follow-up for both the intervention and prospective control comparator groups. Due to the inherent difficulties of administering the HRQoL instruments to new stroke patients, the mRS at Day 0 will be used as a surrogate measure of patient utility in replacement of EQ-5D during the acute phase. This is done to allow the change in quality of life from baseline to 3 and 12 months to be reasonably estimated.

Additionally, the Australian Stroke Clinical Registry (AuSCR) will be used to supplement the clinical or follow-up data for patients admitted with stroke (regardless of intervention), as appropriate (22, 23). Data that can be obtained from AuSCR include patient admission details, acute clinical data, discharge information and HRQoL (using the EQ5D-3L and the mRS) and data on deaths from linkage with the National Death Index. Hospitals participating in the VST program are required to commence data collection for AuSCR by the time they complete the implementation stage to permit the sustainability phase data to be obtained through routine data collection processes (13).

### Identification, Measurement, and Valuation of Costs

The costs included in this analysis comprise intervention costs, direct healthcare, productivity losses/gains and relevant patient out-of-pocket costs. Costs will be valued based on the reference year 2018, and a discount rate of 3% will be applied (24). Table 1 includes a detailed list of resource use items and costs collected and their sources.

**Table 1 T1:** Resource use information collected and sources of unit prices.

**Cost category**	**Unit**	**Data collection method**	**Person responsible for data collection**	**Potential source of unit cost information**
**Acute**				
Telemedicine neurologist time	Minutes	Case Report Form/Neurologist Case Report Form	Site Coordinator/Telemedicine neurologist	Paid invoice, average cost
Diagnostic tests undertaken (regardless of destination)	Type of test	Case Report Form	Site Coordinator	Medicare Benefits Schedule
rt-PA treatment	Dose	Case Report Form	Site Coordinator	Industry
Ambulance transfers (regardless of destination)	Yes/No	Case Report Form	Site Coordinator	Ambulance Victoria
Acute inpatient stay	Bed days	Case Report Form	Site Coordinator	IHPA, National Hospital Cost Data Collection.
**Post-acute**				
Inpatient rehabilitation program	Bed days	Case Report Form	VST Program officers/site coordinator	IHPA, National Hospital Cost Data Collection.
Outpatient rehabilitation services/stroke-related therapy	Type of service, no. of times provided	Follow-up questionnaire	VST Program officers/ site coordinator	Comcare/Medicare Benefits Schedule
Hostel/Nursing home	Length of stay	Follow-up questionnaire	VST Program officers/site coordinator	Aged Care Financing Authority,
Transitional Care	Length of stay	Follow-up questionnaire	VST Program officers/site coordinator	Aged Care Financing Authority
Other hospital re-admissions	Bed days	Follow-up questionnaire	VST Program officers/site coordinator	IHPA, National Hospital Cost Data Collection.
Hospital admission for recurrent stroke recurrence	Yes/No	Follow-up questionnaire	VST Program officers/site coordinator	IHPA, National Hospital Cost Data Collection.
Home modifications	Type of modification	Follow-up questionnaire	VST Program officers/site coordinator	Online search of suppliers
Special equipment and aids	Type of equipment	Follow-up questionnaire	VST Program officers/site coordinator	Online search of suppliers
Medications	Type of medication	Follow-up questionnaires	VST Program officers/site coordinator	Department of Health, Schedule of Pharmaceutical Benefits
**Patient/caregiver**				
Changes in accommodation	Type of accommodation, length of stay	Follow-up questionnaires	VST Program officers/site coordinator	Aged Care Financing Authority
Home modifications	Type of modification	Follow-up questionnaires	VST Program officers/site coordinator	Specified by patient
Special equipment and aids	Type of equipment	Follow-up questionnaires	VST Program officers/site coordinator	Specified by patient
Medications	Type of medication	Follow-up questionnaires	VST Program officers/site coordinator	Department of Health, Schedule of Pharmaceutical Benefits
Informal care	Hours	Follow-up questionnaires	VST Program officers/site coordinator	Fair Work Commission
Outpatient rehabilitation services/stroke-related therapy	Type of service, no. of times provided	Follow-up questionnaires	VST Program officers/site coordinator	Specified by patient
**Societal**				
Changes in workforce participation	Full time/part time/not-working	Follow-up questionnaires	Site coordinator	Australian Bureau of Statistics, average Australian adult wage
**Intervention**				
Cost of maintaining 1,800 line	Usage fee and monthly charge	Program management	VST Program staff at Florey	Paid invoice
Neurologist on-call	Standard on-call rate	Program management	VST Program staff at Florey	Paid invoice
Software upgrades/licensing	Yes/No	Program management	VST Program staff at Florey	Paid invoice
Capital equipment	Yes/No	Program management	VST Program staff at Florey	Paid invoice
Administrative overheads: - Site Coordinator time - Education and training time	EFT Participant time, venue and material costs	Program Management Site Coordinator Education & Training diary	VST Program staff at Florey/site coordinator Site coordinator	Hourly rate Paid invoice

*VAED, Victorian Admitted Episodes Data Set; HACC, Home and Community Care; ABS, Australian Bureau of Statistics; VST, Victorian Stroke Telemedicine; EFT, Equivalent full-time, IHPA, Independent Hospital Pricing Authority*.

Several resource use items relevant to economic evaluations of interventions for stroke (25) are not being collected in order to reduce responder burden and because they are unlikely to have been influenced by the VST Program; these include medical visits in the community, use of medications that are not secondary prevention medication, respite care, volunteer time, and caregiver impacts.

#### Direct Costs of Delivering the Stroke Telemedicine Program

Intervention-related expenses collected via program management processes include the cost for administrative staff including office space, the toll-free telephone line, on-call fees to neurologists, software and licensing costs for the telestroke service, and capital equipment expenses. Local site coordinators were only employed during the set up (~6-months) and implementation (12 month) phases at the hospitals. Their role was to support the clinical implementation and collect data for the research. Only the clinical implementation costs of local site coordinators will be counted as part of the intervention-related expenses. In the second year, these roles were not funded and will not be included in the program delivery (intervention-related) expenses.

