## Abstract

**Introduction:** Telemedicine can address limited access to medical specialists in rural hospitals. Stroke provides an important case study because: it is a major cause of disease burden; effective treatments to reduce disability (e.g., thrombolysis) can be provided within the initial hours of stroke onset; careful selection of patients is needed by skilled doctors to minimize adverse events from thrombolysis; and there are major treatment gaps (only about half of regional hospitals in Australia provide thrombolysis for stroke). Few economic analyses have been undertaken on telestroke and the majority have been simulation models. The aim of this protocol and statistical analysis plan is to outline the methods for the cost-effectiveness evaluation of a large, multicentre acute stroke telemedicine program being conducted in Victoria, Australia.

**Methods:** Using a historical- and prospective-controlled design, we will compare patient-level data obtained in the 12 months prior to the Victorian Stroke Telemedicine (VST) program implementation and during the first 12 months of VST to determine the incremental difference in costs and patient outcomes at 3 and 12 months. Secondary aims include assessing the cost per additional patient receiving intravenous thrombolysis and the cost per additional patient receiving intravenous thrombolysis within 60 min. Tertiary aims include assessing the potential longer-term cost-effectiveness in the second year of the program at the hospitals to determine whether any program benefits are sustained once site coordinators are no longer employed; and modeling the potential net life-time costs and benefits from a societal perspective. Multivariable uncertainty and one-way sensitivity analyses will be performed to assess the robustness of results.

**Results:** Sixteen hospitals participated. Patient-level data collection including 12-month outcomes for the cohorts obtained in the first and second year of the program for each hospital was completed in January 2020.

**Conclusion:** The results from this real-world study with patient-level data will provide high quality evidence of the costs, health benefits and policy implications of telestroke programs, including the potential for application in other locations within Australia or other countries with similar health system delivery and financing.

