Following a pilot period at one hospital in regional Australia, the Victorian Stroke Telemedicine (VST) Program commenced in 2013 and was incrementally expanded to 16 hospitals by 2016 (11, 12). The main features included access to a virtual roster of neurologists for assistance with clinical decision making and employment of a site coordinator in each hospital to integrate the VST protocol into routine emergency department (ED) workflows according to an implementation plan (typically completed within 6 months; with a further 12-months for data collection and support) (13). The establishment of the cost-effectiveness credentials of a state-wide program for Australia, such as VST, is needed since no other states or territories had implemented a coordinated approach to telestroke at the time this study began, and none have used patient-level data to determine cost-effectiveness. This protocol describes the methods for the economic evaluation of the VST program and the statistical analysis plan.

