## Aims

The primary aim of the economic evaluation will be to determine the cost per quality adjusted life year (QALYs) gained at 12 months after stroke.

The secondary aims are to determine the cost per additional patient receiving intravenous thrombolysis and the cost per additional patient receiving intravenous thrombolysis within 60 min of arrival to hospital.

Tertiary aims include assessing the potential long-term cost-effectiveness of the VST Program using data collected during the sustainability period of the study when telestroke had become usual practice. The “sustainability period” was the second year of the telestroke program at the hospitals when the site coordinators were no longer funded to provide direct support for implementing the VST Program. We will also seek to assess the influence of adopting different perspectives (hospital vs. societal) to the measurement of costs and benefits including modeling the potential net life-time impacts.

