### Comparator “Standard Care” Control Cohort

All eligible patients who presented to the ED at a participating hospital during the 12-month period prior to implementation of VST.

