The results of this economic evaluation will inform the decision to develop stroke telemedicine services in other states within Australia. Countries with similar financing and health system models of care may find this information relevant for policy and planning. If deemed cost-effective, the evidence from this study will support expanding telestroke services for improving stroke care and reducing inequities between regional/rural areas and metropolitan locations. Evidence of the sustainability of telestroke services as an effective model for improving the quality of care in the treatment of acute stroke is urgently needed.

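### The second-year ratio is labelled long-term cost-effectiveness but leaves out coordinator cost; call it a running-cost ratio and add a programme-level one

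*Protocol article*

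**What the plan says.** The Introduction names as one of the program's main features the "employment of a site coordinator in each hospital to integrate the VST protocol into routine emergency department (ED) workflows". The section on direct costs of delivering the program limits that employment in time: "Local site coordinators were only employed during the set up (~6-months) and implementation (12 month) phases at the hospitals". It also limits what is charged: "Only the clinical implementation costs of local site coordinators will be counted as part of the intervention-related expenses". The part of the role spent on research data collection is left out. For the following year it states: "In the second year, these roles were not funded and will not be included in the program delivery (intervention-related) expenses".

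The second-year data have two stated purposes. Under Aims, the tertiary objective includes "assessing the potential long-term cost-effectiveness of the VST Program using data collected during the sustainability period of the study". The Abstract words the purpose differently: "to determine whether any program benefits are sustained once site coordinators are no longer employed".

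The only control cohort defined is of patients who presented "during the 12-month period prior to implementation of VST". The Discussion gives the use of the findings: "The results of this economic evaluation will inform the decision to develop stroke telemedicine services in other states within Australia".

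**The concern.** The second-year increment is measured against care before the program existed. It therefore contains whatever lasts from the coordinators' work in set-up and year one. The costing rule keeps that retained benefit in the denominator and removes the cost that produced it from the numerator.

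This does no harm if the result is read as the cost of keeping an established service running. It matters if the result is read as the Aims label it. A jurisdiction that adopts the program cannot reach its second year without first paying for set-up and year one. The Discussion itself explains that telestroke looks better over longer horizons because large early costs are offset by later gains, and an offset requires those costs to stay in the calculation. If the ratio fell between year one and year two, part of the fall could come only from the year in which the coordinator cost is booked.

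**Working it through.** The article gives no coordinator cost, start-up cost or expected QALY gain, so there is no figure of its own to reproduce. The direction can be derived; the size can only be illustrated.

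**Direction.** Let C be the second-year incremental cost per patient under the stated rule, q the second-year QALY gain per patient against the control year, and k the per-patient share of earlier coordinator cost.

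- Ratio under the plan: C/q.
- Programme-level ratio: (C + k)/q.
- Difference: k/q, which is positive whenever k > 0 and q > 0.
- In net-benefit terms at the article's threshold of AUD 50,000 per QALY, the programme-level result is lower by k, or k/50,000 QALY per patient.

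**Spreading the cost.** With K the clinical coordinator cost per hospital and the article's 3% discount rate, the yearly share over T years is K ÷ [(1 − 1.03^−T)/0.03].

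| Programme life T | Annuity factor | Share of K per year |
|---|---|---|
| 2 years | 1.913 | 52.3% |
| 5 years | 4.580 | 21.8% |
| 10 years | 8.530 | 11.7% |

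The plan's second-year share of coordinator cost is 0%.

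**Illustrative size.** Assumptions not in the article: salary AUD 80,000, 100,000 or 120,000 a year; 0.5, 0.8 or 1.0 full-time equivalent; clinical share 25%, 50% or 75%. Employment of about 6 + 12 = 18 months is from the article.

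- Low: 1.5 × 80,000 × 0.5 × 0.25 = AUD 15,000 per hospital.
- Middle: 1.5 × 100,000 × 0.8 × 0.5 = AUD 60,000.
- High: 1.5 × 120,000 × 1.0 × 0.75 = AUD 135,000.

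Two patient counts come from the Discussion: 601 intervention-period patients eligible for detailed audit (601/16 = 37.6 per hospital) and 3,178 with suspected stroke (3,178/16 = 198.6). I treat each as one hospital-year and assume the second year has similar numbers.

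| k per patient-year (AUD) | Low | Middle | High |
|---|---|---|---|
| Audited, 2 years | 209 | 835 | 1,878 |
| Audited, 5 years | 87 | 349 | 785 |
| Audited, 10 years | 47 | 187 | 421 |
| Suspected stroke, 5 years | 16 | 66 | 148 |

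Example: 15,000 × 0.21835 / 37.5625 = 87.

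For audited patients over five years, k/50,000 is 0.0017, 0.0070 and 0.0157 QALY. With an assumed gain of 0.01 to 0.05 QALY per patient, k/q runs from 15,000 × 0.21835 / 37.5625 / 0.05 = AUD 1,744 to 135,000 × 0.21835 / 37.5625 / 0.01 = AUD 78,477 per QALY. With the suspected-stroke denominator and the same assumed gains, it runs from AUD 330 to AUD 14,841. The sign is fixed; the size depends on inputs that the article does not give.

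**The case against.** The strongest defence is that the exclusion is open and accurate. The roles were not funded in the second year, so no such cost arose. The Abstract asks whether benefit lasts without coordinators, and for that question a second year costed without them is the coherent choice. This stands: the second-year ratio is valid for what it measures, and only its label and use need care.

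A reader might infer more than the article supports:

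- **That the second-year ratio will look better than the first.** Whether benefit persists is what that year tests. If it wanes, the ratio need not improve. The understatement is only relative to a second-year ratio that carries the earlier cost.
- **That neither year informs roll-out.** The main comparison is the pre-VST year against the first 12 months of VST, where clinical coordinator cost is counted. That is usable by a new adopter.
- **That year one overstates the cost per QALY because capital and training fall wholly in it.** The article removes only coordinator roles from year two. The paid invoices in Table 1 are listed as a source of unit costs and are not a rule for allocating cost to years. A spreading rule may stand in a fuller plan.
- **That the lifetime result drops start-up cost.** The Long-Term Modeling section mentions implementation costs to be offset. It does not say which year's cost set enters the model, so the omission is not shown.

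The illustrative amounts are also open to challenge. A two-year spread gives the largest share, and the suspected-stroke denominator cuts the per-patient figure to about one fifth.

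**Conclusion.** The point holds as a cheap improvement, not as an error in the costing. The Aims attach a long-term label to a comparison from which the costing section removes coordinator cost, while the pre-VST comparator keeps any benefit that this cost bought. With a positive QALY gain, the result is too low if read as the long-term cost per QALY for a new adopter. It remains correct as a running-cost figure for established sites.

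The size cannot be derived from the article. The illustrative range of AUD 87 to 785 per audited patient-year rests on assumed salaries, working fractions and clinical shares, a five-year life, and similar patient numbers in the second year. It shows that the effect could be negligible or could matter at the AUD 50,000 threshold.

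**What to change.** 1. Label the second-year-only ratio 'running cost once established', and tie it to the sustainability question in the Abstract.
2. Add a programme-level ratio for the long-term aim. It should include the clinical share of set-up and first-year coordinator cost, either spread at the 3% discount rate over a stated programme life that is varied in sensitivity analysis, or pooled over first- and second-year patients.
3. State that the lifetime Markov model includes this start-up cost.

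The cost is some wording and one further calculation, because the article already plans to collect coordinator time and its clinical share. The downsides are a less favourable long-term ratio and a programme life that must be assumed.

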#### Direct Healthcare Costs of Participants

Resource use during the acute phase is captured via auditing of patient medical records. Neurologist consultation time via telestroke is captured through the Neurologist Consultation Form. To estimate the hospital costs, we will access published national hospital cost data (Table 1). The national efficient price for the stroke/TIA diagnostic-related group (DRG) categories will be mapped to each patient based on diagnosis, severity on presentation, length of stay and discharge destination.

Follow-up questionnaires were administered to the intervention and prospective control groups at 3- and 12-months post discharge to collect resource use information and other costs incurred during the post-acute hospital phase. Participants were asked to provide information on changes in accommodation, hospital re-admissions, stroke recurrence, and other ongoing stroke-related resource use such as outpatient rehabilitation services, medications, home modifications, equipment and aids purchased.

#### Productivity and Informal Care (Indirect) Costs

Information on informal care and changes to employment were collected at 3- and 12-months post discharge to estimate indirect costs. Productivity losses or gains of patients will be calculated based on the average earnings by age and gender available from the Australia Bureau of Statistics (26). Hours of informal care will be valued using published average unit costs of formal caregivers.

### Data Analysis

The data analyses will be performed using Microsoft Office Excel or STATA software (StataCorp. 2019. State Statistical Software: Release 16. College Station, TX: StataCorp LLC), with add on software as required for probabilistic multivariable analysis. Descriptive statistics, using parametric and non-parametric methods appropriate for the data will be used to summarize the pooled data for the control (pre-implementation) and intervention cohorts. Multivariable or multilevel models (with level defined as hospitals) will also be undertaken. For example, generalized linear regression modeling of costs with gamma distributions and log linked for multivariable analyses that adjust for age, gender, stroke-type, stroke severity, length of stay and patient clustering by hospital as part of the cost-description analyses may be appropriate to account for the non-parametric cost data. The results will then be used as inputs in the incremental cost-effectiveness and cost-utility analyses.

Multiple imputation methods and population weighted adjustment methods will be applied to address the missing data for variables that are found to have a large impact on the healthcare services costs (27).

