## Methods

### Design

The economic evaluation, a sub-study of the clinical effectiveness project (12), will be a pragmatic, real-world, economic evaluation of the implementation and long-term impacts of the VST Program compared to standard care. The study design of the VST Program evaluation has been detailed previously (11–13). In brief, the study has a pre-post-test design with a combination of historical- and prospective-control patient-level data to provide evidence on standard care practice, made possible through the iterative addition of hospitals over 7 years. After training and a short pilot phase to refine the clinical protocol at each hospital, the VST Program was implemented and clinicians then have the ability to consult with a virtual network of stroke specialist doctors for diagnosis and treatment recommendations for patients presenting to their emergency departments (EDs) with suspected stroke (13). Prior to the VST Program commencing, only five of the 16 hospitals were routinely providing intravenous thrombolysis for patients with ischaemic stroke. The project is led by the Florey Institute of Neuroscience and Mental Health. As part of this sub-study, a cost-description analysis of each comparator (pre-post) pathway will be undertaken and then compared to determine the incremental cost-effectiveness and cost-utility of the VST Program (see below).

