### Sample Size

The sample size for the economic evaluation is dependent on the number of patients presenting to the participating hospitals who meet the inclusion criteria. Data collected on over 1,000 patients will be available for the economic evaluation.

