The strengths of our methods for this economic evaluation include the reliable patient-level data in the acute phase and detailed intervention costs. The final sample sizes for the clinical effectiveness study as of 31 December 2017 were 2,887 patients with suspected stroke in the control period and 3,178 patients with suspected stroke in the VST intervention period. There were no major differences in patient characteristics with suspected stroke between study periods, however more were provided an initial diagnosis of ischaemic stroke and had a documented time from symptom onset in the VST Program implementation cohort (13). The number of eligible patients for detailed audit was 423 for the control period and 601 in the intervention period (13). As of January 2019, 360 of the 764 eligible patients who could be sent an outcome survey at 3-months have provided survey responses following hospital admission (26 patients in the control period and 334 patients in the intervention period). Information from another 101 patients have been collected at 12 months after their hospital admission (88 in the control period and 13 in the intervention period).

Another strength of the economic evaluation will be the use of the EQ-5D to calculate the utility score for estimating QALYs gained. This will allow VST results to be compared with international studies which often use the EQ-5D instrument. In a recent review, there were very few well designed economic evaluations that could be used to usefully inform public health policy and investment decisions in general, highlighting an urgent need for greater application of economic evaluation to understand the cost-effectiveness of alternative implementation efforts (36). Our work will be an important contribution to the field of stroke and implementation research that is focused on improving uptake of evidence-based interventions in hospital settings.

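### The only cost model the plan exemplifies adjusts for length of stay; if it supplies the incremental cost, any change in stay caused by the program is adjusted out of the ICER

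*Protocol article*

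**What the plan says.** All references are to the protocol article.

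- **Data Analysis** names one cost model by way of example: a generalized linear model with gamma distribution and log link that would "adjust for age, gender, stroke-type, stroke severity, length of stay and patient clustering by hospital as part of the cost-description analyses". The plan says that such a model "may be appropriate to account for the non-parametric cost data".
- The next sentence gives the destination: "The results will then be used as inputs in the incremental cost-effectiveness and cost-utility analyses".
- **Design** makes the same link: "a cost-description analysis of each comparator (pre-post) pathway will be undertaken and then compared to determine the incremental cost-effectiveness".
- **Table 1**, acute rows, counts the hospital stay in days: "Acute inpatient stay Bed days Case Report Form".
- **Direct Healthcare Costs of Participants** says that the hospital price is "mapped to each patient based on diagnosis, severity on presentation, length of stay and discharge destination".
- **Sensitivity Analyses** varies unit costs, quantities, mRS outcome and QALYs. It lists no analysis with length of stay left out.

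**The concern.** An ICER needs the total difference in cost between the two pathways. Length of stay is not a baseline confounder of that difference. The program acts in the emergency department, and the stay follows, so the program could change it. Length of stay is also a component of the dependent variable, through the bed-day count and the price mapping. A cohort coefficient that holds stay constant estimates the cost effect net of any change in stay, which is a different quantity.

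The numerator of the primary aim, cost per QALY at 12 months, is at stake. A program that shortens stay would look more expensive than it is, and one that lengthens stay would tend to look cheaper. A bootstrap or acceptability curve built on such an increment would carry the same distortion.

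**Working it through.** **1. The plan's own figure.** The Sample Size section says: "Data collected on over 1,000 patients will be available for the economic evaluation". The Discussion says: "The number of eligible patients for detailed audit was 423 for the control period and 601 in the intervention period". 423 + 601 = 1,024, so the two agree. The plan gives no incremental cost, length of stay, bed-day price or program cost per patient, so no plan figure for the increment can be reproduced.

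**2. What the covariate removes.** Let P be the program cost per patient, c the cost per bed day, d the program's effect on mean stay in days, and r its effect on all other costs.

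- Total increment = P + c × d + r
- Increment with stay held constant = P + r (on an additive scale)
- Difference = c × d

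With r = 0, the sign changes when d is negative and c × |d| exceeds P.

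**3. Illustration.** Taken from the documents: group sizes of 423 and 601, gamma model with log link. Assumed, not from the documents:

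- control mean stay 8 days, gamma with shape 1.5, minimum 1 day, dependent on severity;
- c = AUD 1,500; other cost gamma with mean AUD 3,000; r = 0;
- P = AUD 500, 1,000 or 2,000;
- d from -2 to +2 days.

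Each scenario has 60 simulated datasets. The increment is the mean predicted cost with everyone in the program minus the mean with everyone in control, adjusted for severity. Results for P = 1,000, in AUD:

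| d (days) | P + c × d | Model without stay | With stay, linear | With log stay |
|---|---|---|---|---|
| -2 | -2,000 | -1,848 | +1,365 | +1,188 |
| -1 | -500 | -387 | +1,536 | +1,286 |
| 0 | +1,000 | +1,189 | +1,555 | +1,461 |
| +2 | +4,000 | +3,898 | +1,817 | +1,608 |

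The standard deviation across datasets for the model without stay is 453 to 662 in these rows. The Monte Carlo error of those means is therefore about 58 to 85 (453/√60 to 662/√60).

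**4. Sign.** Of the 21 combinations of d and P, 6 have a bed-day saving larger than P: d = -2 with each P, d = -1 with P = 500 or 1,000, and d = -0.5 with P = 500. In those 6 the model without stay gave a negative increment and both models with stay gave a positive one. In the other 15 the sign did not change. For example, at d = -1 and P = 2,000 the increment went from +583 to +2,940 (linear) or +2,558 (log), an overstatement without reversal.

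**5. How much is not the stay pathway.** With d = 0 there is no change in stay to remove, yet the models with stay exceed the model without it by 1,555 - 1,189 = 366 and 1,461 - 1,189 = 272. This is misfit of a multiplicative link to additive costs. It can offset the main effect when d is small: at d = +0.5 and P = 2,000 the models with stay gave +3,071 and +2,807, against +2,783 without.

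**6. A second set of assumptions.** With c = 2,000, other cost 3,000, P = 1,000, stay 8 versus 7 days and 200 datasets, the increment was -939 without stay, +1,471 with linear stay and +1,312 with log stay. The cost effect with stay fixed is 1,000 by construction, so 471 and 312 of those values are again misfit.

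**7. What drives the size.** Bed days make up 12,000/15,000 = 80% of control cost in step 3 and 16,000/19,000 = 84% in step 6. Those shares are assumptions. The further costs in Table 1 (rehabilitation, residential care, informal care, workforce participation) are not modelled separately.

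**The case against.** The strongest reply is that nothing is fixed. The model is introduced as an example and hedged, it sits within the cost-description analyses, and a condensed article may leave the final covariates to a fuller plan. Using length of stay to describe what drives cost is legitimate. The sentence on inputs follows a paragraph that also covers descriptive statistics and other models, and it does not name the stay-adjusted coefficient as the ICER numerator.

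Part of this stands. A reader might infer that the plan commits to a stay-adjusted increment; the wording does not go that far. But this is the only covariate set shown, the results are sent forward without exception, and Design says that the cost-description pathways are what is compared. The descriptive label therefore does not keep the model out of the ICER.

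Three other stronger readings also fail:

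- **That stay is the main driver of cost.** No section ranks it, and a 12-month societal total includes many other items.
- **That the adjusted coefficient is mostly program cost.** Post-acute cost changes not explained by stay would remain in it (the term r above).
- **That the ICER will have the wrong sign, or that bias vanishes exactly when stay is unchanged.** Reversal needs a bed-day saving larger than the other cost increases, for which the documents give no figure. The log link leaves a gap even when stay is unchanged.

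**Conclusion.** The point holds conditionally. If the exemplified model supplies the incremental cost, it estimates the cost effect net of any change in stay, which is not the quantity an ICER needs. On an additive scale the bias is the bed-day cost times the program's effect on stay. It can hide a saving or understate an added cost, and it can change the sign when the bed-day saving exceeds the program cost and any other cost increases. In the one-day-shorter illustration the estimate rises by 387 + 1,536 = AUD 1,923 (linear) or 387 + 1,286 = AUD 1,673 (log), against a stay component of 1,500. These figures rest wholly on assumed inputs and show direction and mechanism, not the expected size in this study. Because the primary numerator is affected and no listed sensitivity analysis would reveal the problem, it should be settled before the analysis is run.

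**What to change.** - Remove length of stay from every model whose results feed the incremental cost or the ICER.
- In those models, adjust only for characteristics fixed at presentation: age, sex, stroke type, severity on presentation and pre-stroke mRS. The last is not in the example list, but Data Collection shows that pre-morbid function is already audited. Keep the allowance for clustering by hospital.
- If a model with length of stay is wanted, label it a descriptive analysis of cost drivers and state that it is not used in the ICER.

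The cost is one line in the plan and one covariate in the code. No new data are needed.
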